# Effectiveness of personalised, home-based nutritional counselling on infant feeding practices, morbidity and nutritional outcomes among infants in Nairobi slums: study protocol for a cluster randomised controlled trial

**DOI:** 10.1186/1745-6215-14-445

**Published:** 2013-12-27

**Keywords:** Breastfeeding, Infant feeding practices, Child nutrition, Cluster randomised controlled trials, Kenya, Sub-Saharan Africa, Urban slums

## Abstract

**Background:**

Nutrition in the first 1,000 days of life (during pregnancy and the first two years) is critical for child growth and survival. Poor maternal, infant and young child nutrition (MIYCN) practices are widely documented in Kenya, with potential detrimental effects on child growth and survival. This is particularly a problem in slums, where most urban residents live. For example, exclusive breastfeeding for the first six months is only about two per cent. Innovative strategies to reach slum residents are therefore needed. Strategies like the Baby Friendly Hospital Initiative have proven effective in some settings but their effectiveness in resource-limited settings, including slums where many women do not deliver in hospital, is questionable. We propose to test the effectiveness of a home-based intervention on infant feeding practices, nutrition and health outcomes of infants born in two slums in Nairobi, Kenya.

**Methods/Design:**

The study, employing a cluster-randomised study design, will be conducted in two slums in Nairobi: Korogocho and Viwandani where 14 community units (defined by the Government’s health care system) will form the unit of randomization. A total of 780 pregnant women and their respective child will be recruited into the study. The mother-child pair will be followed up until the child is one year old. Recruitment will last approximately one year and three months from September 2012 to December 2013. The mothers will receive regular, personalised, home-based counselling by trained Community Health Workers on MIYCN. Regular assessment of knowledge, attitudes and practices on MIYCN will be done, coupled with assessments of nutritional status of the mother-child pairs and diarrhea morbidity for the children. Statistical methods will include analysis of covariance and multinomial logistic regression. Additionally, cost-effectiveness analysis will be done. The study is funded by the Wellcome Trust and will run from March 2012 to February 2015.

**Discussion:**

Interventions aimed at promoting optimal breastfeeding and complementary feeding practices are considered to have high impact and could prevent a fifth of the under-five deaths in countries with high mortality rates. This study will inform policy and practice in Kenya and similar settings regarding delivery mechanisms for such high-impact interventions, particularly among urban poor populations.

**Trial registration:**

ISRCTN83692672

## Background

Despite reduction of undernutrition being one of the Millennium Development Goals (MDGs) targets, undernutrition continues to be a great public health concern in many developing countries, particularly in sub-Saharan Africa (SSA) [1]. Millions of children globally suffer from undernutrition despite many declarations and action plans aimed at combatting the phenomenon. A total of 165 million, 101 million and 51 million children under the age of five are estimated to be stunted, underweight and wasted, respectively. What is more worrying is the high level of malnutrition in SSA, where approximately 40% of all children aged less than five years (56 million) are estimated to be stunted [2]. Undernutrition is a serious risk factor for ill health, and contributes substantially to the burden of disease in developing countries. It is associated with more than half of all child deaths, and is responsible for 15% of the total loss in disability-adjusted life years (DALYs) in countries with high child mortality [3,4]. Increasingly, adverse ramifications of childhood undernutrition are recognized later in the life course. These include impaired cognitive development and poor educational achievement; low economic productivity; obesity in adulthood and a consequent risk for metabolic disease [5-8].

There is a growing recognition of the importance of nutrition in the first 1,000 days of life (during pregnancy and the first two years) with regard to child growth, health and survival. In 2002, the World Health Organization (WHO) and the United Nations Children’s Fund (UNICEF) jointly developed the global strategy for infant and young child nutrition (IYCN), which aims to revitalize efforts to promote, protect and support appropriate infant and young child feeding, thereby working towards alleviating the burden of disease associated with malnutrition among the world’s children [9]. The strategy builds on past initiatives such as the Innocenti Declaration of 1990 and the Baby-friendly Hospital Initiative (BFHI) launched in 1991. The WHO recommends exclusive breastfeeding in the first six months of life, followed by extended breastfeeding for two years or beyond, coupled with timely, nutritionally adequate, safe and appropriately fed complementary foods for optimal growth of the child. The global strategy on IYCN highlights the notion that inadequate knowledge about proper foods and feeding practices is often a more important determinant of malnutrition than the availability of food [9,10]. It is estimated that interventions that promote optimal breastfeeding and complementary feeding could prevent about a fifth of the under-five deaths in countries with high mortality rates [11,12].

Poor breastfeeding and complementary feeding practices have been widely documented in the low- and middle-income countries (LMICs), where only about 39% of infants are exclusively breastfed for the first six months. In Kenya, like in other LMICs, although almost all children are breastfed, poor maternal, infant and young child nutrition (MIYCN) practices are widely documented. However, some recent positive change in early infant feeding practices has occurred as in the 2008/2009 Kenya demographic and health survey (KDHS), 32% of children are recorded as exclusively breastfed for six months, an improvement from 13% in 2003, as reported in KDHS 2003 [13,14]. Additionally, only 39% of children aged 6 to 23 months are fed according to IYCN guidelines [15,16], and maternal nutrition is widely influenced by cultural beliefs and practices. Consequently, substantial levels of child malnutrition and poor child health and survival have been documented in Kenya, including high levels of stunting (35%) among children less than five years of age [13].

To address the problem of child malnutrition, the Kenyan Government developed a strategy in 2007, mirroring the WHO/UNICEF global strategy for IYCN, aimed at promoting optimal IYCN practices in the country [9,17]. The strategy is implemented mainly through the BFHI, which promotes breastfeeding in maternity wards around the time of delivery. Although there has been some improvement in the proportion of children exclusively breastfed in the last few years, the impact of this hospital-based initiative in low-income countries like Kenya is questionable. This is because most women, especially the poor, deliver at home and IYCN practices are greatly influenced by traditional beliefs and practices [13,18]. For example, in Kenya, only 42% of women deliver in health facilities, and this has not changed much in the last 20 years [13].

Urban poor settlements are expanding at an alarming rate in SSA, with the majority of urban residents living in slum settlements [19], thus presenting a unique challenge with respect to implementing the IYCN strategy in Kenya. These slums have been marginalized with regard to provision of Government services; hence public health facilities are rare. Additionally and consequently, a substantial proportion of slum women do not deliver at health facilities, while others deliver in sub-standard private health facilities; only 48% deliver in facilities with skilled birth attendants [20,21]. This means that many of these women do not benefit from the counselling on IYCN offered through BFHI. Findings from studies done in the urban slums of Nairobi indicate high levels of suboptimal MIYCN practices and malnutrition. For example, only two per cent of infants are exclusively breastfed for the first six months, while 15% of infants stop breastfeeding by the end of one year [22]. Furthermore, about four in ten children under the age of five are stunted [23]. This level of malnutrition in an urban setting may not entirely be due to poverty but may reflect practices that might be addressed with proper counselling and advice.

The aim of this cluster randomised controlled trial is to test the effectiveness of personalised, home-based nutritional counselling of pregnant and lactating mothers by Community Health Workers (CHWs) on MIYCN practices, and consequently on morbidity and nutritional outcomes of infants in two Nairobi slums. Specifically, we aim to determine: (i) the effect of the intervention on breastfeeding and complementary feeding knowledge, attitudes and practices among mothers of infants; (ii) the effect of the intervention on nutritional outcomes among infants; (iii) the effect of the intervention on morbidity from diarrhea among infants; (iv) the experiences, and facilitating and limiting factors associated with the intervention; and (v) the cost-effectiveness of the intervention. The primary objective is to change breastfeeding practices, particularly to improve the rate of exclusive breastfeeding, which is currently extremely low in the slums [22], despite its documented importance in child survival [11]. The primary hypothesis is that personalised, home-based nutritional counselling and support of mothers in Nairobi slums by CHWs will lead to higher knowledge and self-efficacy in breastfeeding, thereby resulting in adherence to WHO guidelines for breastfeeding. This is expected to lead to improved rates of exclusive breastfeeding for six months. The CHWs will therefore counsel mothers on what they should do regarding breastfeeding and other maternal MIYCN practices and how they should do it including breast positioning and attachment and expressing breast milk, which is expected to lead to higher knowledge and self-efficacy. The proposed strategy (community-based initiative), backed by the Ministry of Health, builds on the existing MIYCN strategy by the Government and is expected to get over the problem of women having to present at hospitals to receive information. This is important for urban poor women who have limited health care access [20,21]. The backing by the Government is critical for potential scale-up of the strategy within the Kenyan health care system if it proves to be successful in the trial.

## Methods/Design

### Study setting

The study will be carried out in two slums of Nairobi, Kenya (Korogocho and Viwandani) where the African Population and Health Research Center (APHRC) runs the Nairobi Urban Health and Demographic Surveillance System (NUHDSS), covering close to 70,000 residents (Figure 1). The two slum areas are densely populated with 63,318 and 52,583 inhabitants per square km, respectively, and are characterized by poor housing, lack of basic infrastructure, violence, insecurity, high unemployment rates, and poor health indicators [24]. The two slums are located about 7 km from each other. The NUHDSS involves a systematic quarterly recording of vital demographic events, including births, deaths and migrations occurring among residents of all households in the NUHDSS area since 2003. Other data, including household assets, morbidity, and education among others, are also collected and updated regularly. More information regarding the study area and the NUHDSS can be obtained from previous publications [25].

**Figure 1 F1:**
[figure not shown]
**Maps of the study areas (Korogocho and Viwandani).** Source: Emina *et al*. 2009 [25].

### Study design and randomization

The study will adopt a cluster-randomised trial design [26,27]. For pragmatic purposes, community units (CUs), defined by the Government’s Community Strategy, will be used as the clusters. Fourteen CUs have been defined in the study areas: eight in Korogocho and six in Viwandani. These CUs will be randomised with half allocated to the intervention and the other half to the control arm. The random sequence of allocation of the CUs to the intervention or control arm will be computer-generated. The clusters will be stratified with regard to two aspects before randomization: slum of residence (Korogocho and Viwandani) and number of women of reproductive age in each cluster: large clusters and smaller clusters. Those in the same slum and in the same strata with regard to size will be randomly allocated to either intervention or control group. Cluster randomization is preferred over individual-level randomization to minimize contamination and for pragmatic purposes in case of future scale-up of the intervention. Randomization will be done by a data analyst who is not a primary member of the study team.

### Clusters and study populations

Community units (CUs) in Korogocho and Viwandani that fall within the NUHDSS area will constitute the clusters to be included in the study. CUs are geographically defined units, mostly equal to a village (in our study setting) and usually have a population size of approximately 5,000 people. The CUs are defined by the Community Strategy, a Government community-based approach where CHWs provide health care services to people at the community level. The reason for choosing to work with the defined CUs is pragmatic because they are administrative areas that are defined by the health care system and any intervention moving forward in the future would need to map onto these administrative units to be effective.

Study participants will include all pregnant women aged between 12 to 49 years old, who are residents of CUs in Korogocho and Viwandani slums that fall within the NUHDSS area, and their respective children (when born). These will be recruited during pregnancy on a rolling basis until the desired sample size is achieved. The target is to recruit the women as early as possible during pregnancy, particularly during the first or second trimester. While the reproductive age in most studies is usually defined as 15 to 49 years, we include girls aged 12 to 14 years because a substantial proportion (close to 10%) of adolescents in the study areas is sexually active before the age of 15 years [28].

To be excluded from the study will be: (a) women of reproductive age who will have given birth before the proposed intervention starts; (b) women with a disability that makes delivery of the intervention difficult (for example, a hearing or sight problem, or mental handicap).

To be dropped from the analysis will be: (a) women who lose the pregnancy and/or have a still-birth; (b) women who are lost to follow-up during pregnancy; and (c) mother-child pairs of children with a disability.

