The elements of counselling package are based on WHO/UNICEF IYCF guidance documents, training and other materials, including the Infant and Young child feeding counselling integrated course [32]. The package is designed to equip community workers or primary health care staff to be able to support mothers, fathers and other caregivers to optimally feed their infants and young children. The CHWs will be equipped with infant and young child feeding counselling cards; brightly coloured illustrations that depict key infant and young child feeding concepts and behaviours for the CHWs to share with mothers, fathers and other caregivers. The package will be adapted to include counselling messages on maternal nutrition.

Counselling will be initiated during pregnancy as soon as the mother is recruited and will be continued until the end of infancy (one year after delivery). Counselling will encompass maternal nutrition, immediate initiation of breastfeeding after birth, breast positioning and attachment, exclusive breastfeeding, frequency and duration of breastfeeding, expressing breast milk, storage and handling of expressing and lactation management. It will also focus on age-appropriate complementary feeding, starting at six months: age appropriate complementary foods (nutritious, safe, affordable, and locally available), feeding frequency and quantity, and appropriate feeding practices including hygiene and responsive feeding behaviours, which encourage mother-child interaction during feeding [33,34]. For the intervention arm, CHWs will visit the pregnant woman about once every month up to week 34, after which they will visit the mother weekly until delivery. After delivery, they will visit the mother weekly in the first one month, then once a month until the end of infancy, but during the fifth month when mothers are expected to initiate complementary feeding, the frequency will be biweekly.

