### Statistical analysis

Determination of change for the primary outcome (exclusive breastfeeding) will be done at month six. Difference in duration of exclusive breastfeeding will also be determined longitudinally up to six months between the intervention and control groups. Comparison for other outcomes such as morbidity from diarrhea and malnutrition will be done longitudinally at around month three, six, nine and twelve. Analyses will involve a comparison of differences in the intervention and control groups with regard to the primary outcome (exclusive breastfeeding) and secondary outcomes (other infant feeding practices, diarrhea morbidity and nutritional outcomes), controlling for baseline measures (for example, previous breastfeeding practices) and prognostic factors (for example, Socio-economic status (SES) and household food security) if randomization of the clusters does not control for differences in these factors at baseline. Statistical methods to determine change will include analysis of covariance (ANCOVA) for continuous variables (for example, duration of exclusive breastfeeding and any breastfeeding and multinomial logistic regression analysis for categorical variables (that is, whether exclusively breastfed for six months or not) [40]. Additionally, survival analysis (proportional hazard analysis) for variables measured longitudinally (for example, duration of breastfeeding and malnutrition and multilevel modelling for repeated measures such as diarrheal morbidity will be applied. Intention-to-treat analysis [41] will be applied as appropriate. Efforts will be made to maximize follow-up of participants, using the NUHDSS framework to minimize missing information. Quantitative data analysis will mostly be done using Stata version 12.1. (StataCorp LP, College Station, Texas, USA). (See Table 2 for detailed outline of data analysis plan).

**Table 2 T2:** Data analysis outline

**Study objective**	**Outcome variables**	**Independent variable**	**Control variables**	**Type of analysis**
1. To determine the effect of the intervention on breastfeeding and complementary feeding knowledge, attitudes and practices among mothers of infants	1. Knowledge and attitude levels on breastfeeding and other infant feeding practices	Intervention status	SES^1^, food security, maternal demographic characteristics, antenatal care child morbidity	Multinomial logistic regression for rates and survival analysis for duration

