Other than just assessing the effectiveness of the interventions on breastfeeding and other infant feeding practices, this study will also determine the effectiveness of the intervention on other outcomes including morbidity from diarrhea and nutritional outcomes [48,49,52]. Studies elsewhere have indicated the effectiveness of interventions aimed at promoting breastfeeding on these outcomes. A good example of a study where these effects have been studied is the PROBIT (Promotion of Breastfeeding Intervention Trial) study in Belarus in 1996 to 1997 that involved slightly over 17,000 mother-child pairs. That study showed a significant reduction in the risk of gastrointestinal infections and a positive effect on growth of infants. The prevalence of gastro-intestinal infections was 9% in the intervention group compared to 13% in the control group (OR = 0.6; CI: 0.40-0.91; *P* <0.05). Likewise, infants in the intervention group were 106 g and 89 g heavier; and 0.50 and 0.46 cm taller at three and six months respectively compared to children in the control group (*P* <0.05) [49,52]. The effects may be related to optimal breastfeeding and other infant feeding practices on growth and morbidity.

Some limitations to this study may include bias in reporting of the primary outcome (exclusive breastfeeding). To counter this, objective breast milk analysis using the stable isotope technique will be used. It is possible that even with randomization of clusters, there will be difference in the baseline measures in the intervention and control group by chance. Analysis methods to be adopted will control for baseline differences. Additionally, given high mobility in the urban slums, some of the participants may be lost to follow-up, while some may also move to alternative group clusters. To counter this, intention to treat analysis will be adopted, while an allowance for loss to follow-up has been included in the sample size determination.

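### Dropping women lost in pregnancy and pairs with a disabled child conflicts with the stated intention-to-treat analysis, and the disability exclusion discards outcomes that can be observed

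*Protocol article*

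**What the plan says.** The section on clusters and study populations has two separate lists. One sets out who is not eligible. The other concerns women already in the study: "To be dropped from the analysis will be: (a) women who lose the pregnancy and/or have a still-birth", followed by "b) women who are lost to follow-up during pregnancy; and (c) mother-child pairs of children with a disability". The article does not define disability, and it describes no blinded assessment of it.

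The Statistical analysis section says "Intention-to-treat analysis [41] will be applied as appropriate" and does not define the set. On missing data it offers prevention: "Efforts will be made to maximize follow-up of participants, using the NUHDSS framework to minimize missing information". The limitations paragraph of the Discussion notes that "some of the participants may be lost to follow-up, while some may also move to alternative group clusters" and answers: "To counter this, intention to treat analysis will be adopted, while an allowance for loss to follow-up has been included in the sample size determination".

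On timing, the community units are allocated at random, women are then recruited on a rolling basis, and "Counselling will be initiated during pregnancy as soon as the mother is recruited".

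**The concern.** Intention-to-treat keeps enrolled participants in the arm to which they were allocated, whatever happens later. The second list removes participants because of what happens later. An analyst cannot follow both instructions, and a reader of the results would not know which one had been followed.

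What is at stake is the comparability of the arms for the primary outcome, exclusive breastfeeding for six months. Exclusions that follow allocation, and may follow counselling, can select different women in the two arms. Home visits by community health workers are more frequent in the intervention arm than in control, so retention in pregnancy, or recognition of a child's disability, could in principle differ by arm. Pregnancy loss and still-birth are a different matter: no infant exists whose feeding could be measured.

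**Working it through.** **Step 1: the rules side by side.**

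- *Child with a disability.* The child is alive and the mother can be interviewed, so the primary outcome can be observed. The exclusion rests on an undefined condition judged after exposure. It contradicts intention-to-treat on any reading.
- *Woman lost during pregnancy.* No outcome is observed. Keeping her needs a missing-data approach, and dropping her is a complete-case rule. Intention-to-treat as a principle supplies no outcome for her.
- *Pregnancy loss or still-birth.* No feeding outcome exists. The exclusion is defensible, provided the numbers are shown by arm.

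**Step 2: what the sample-size allowance does.** Inputs from Sample size considerations: 2% against 12%, two-sided 5%, power 80%, minimum 196 in both arms together, design effect 3.2, attrition 20%, about 780 pairs.

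- Per arm, unpooled: (1.96 + 0.84)² × (0.02 × 0.98 + 0.12 × 0.88) / 0.10² = 98.3, or about 196 in total. This matches.
- 196 × 3.2 = 627.2, and 627.2 / 0.8 = 784. This matches about 780.

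The allowance divides the target by 0.8. It protects precision and does nothing about selective loss.

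**Step 3: possible size, on assumed shares.** The article does not say how much of the 20% falls in pregnancy, or how many children would have a disability. Let d be the share dropped, p the rate among retained pairs (12% and 2%) and r the rate among dropped women. The all-women difference is

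[p_T(1 − d_T) + r_T·d_T] − [p_C(1 − d_C) + r_C·d_C].

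| Dropped, intervention / control | Rate among dropped women | All-women rates | Difference |
|---|---|---|---|
| any | same as retained in each arm | 12% v 2% | 10.0 points |
| 10% / 10% | 0 | 10.8% v 1.8% | 9.0 |
| 20% / 20% | 0 | 9.6% v 1.6% | 8.0 |
| 10% / 20% | 0 | 10.8% v 1.6% | 9.2 |
| 20% / 10% | 0 | 9.6% v 1.8% | 7.8 |

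The 10 points among retained pairs overstate the all-women difference by 0 to 2.2 points.

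**Step 4: no true effect.** Suppose 2% of all women in both arms breastfeed exclusively, and dropped women never do. With 20% dropped in intervention and 10% in control, the retained rates are 0.02/0.8 = 2.5% and 0.02/0.9 = 2.2%, a spurious difference of about 0.3 points. At this base rate, such dropping would mostly distort the size of an effect and would hardly create one.

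**The case against.** The strongest reply is that the exclusions are fixed in advance, apply equally to both arms, and could be called a modified intention-to-treat set. That would settle the label. It would not justify discarding observable outcomes for children with a disability, and the article uses no such label.

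A second reply concerns the Discussion sentence. It names two problems and gives two responses, so intention-to-treat may be meant for movement between clusters and the sample-size allowance for loss. That reading is fair. Even so, the sentence adopts intention-to-treat without qualification, and the allowance does not remove bias from loss. The softer wording in the Statistical analysis section does not say which exclusions are compatible with it.

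Several stronger readings are tempting and are not supported:

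- *The whole primary comparison becomes a completer analysis.* The rule covers women lost before birth. It does not order pairs lost after birth to be dropped.
- *The 20% attrition (156 of 780) is the share dropped.* It is an allowance for total attrition, and follow-up runs until the child is one year old. No share for pregnancy is given.
- *Loss differs by arm.* Counselling visits differ, but study questionnaires are two-monthly and retention uses the surveillance system, with no arm difference stated for either. Differential loss is possible and is not shown.

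One further objection limits the remedy. For a woman lost in pregnancy it may be unknown whether a live birth occurred, so imputing a feeding outcome for all such women would include pregnancies with no infant. Events are also few: 627.2 / 2 × 0.02 is about 6 in the control arm, over seven clusters. An elaborate within-arm imputation model is therefore debatable and can be left to the SAP.

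**Conclusion.** The conflict between the exclusion list and the intention-to-treat statements is real and should be resolved before analysis. The disability exclusion is the firm part: it discards observable primary outcomes on an undefined, post-exposure condition. For women lost in pregnancy, the fault is that a complete-case rule stands beside an intention-to-treat claim, with only prevention offered against missing outcomes.

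Bias is possible and its size is unknown. The range of 0 to about 2 points rests on assumed dropping of 10–20% per arm and on lost women doing no better than retained women. Zero applies if they respond like retained women, and about 2 points if none breastfed exclusively. A reader might infer that the trial's result will be biased, or that a completer result will be passed off as intention-to-treat. The document supports neither as a prediction.

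**What to change.** - Delete the disability exclusion. Keep these pairs in the primary analysis, in the arm of the cluster where they were recruited, and exclude them only in a sensitivity analysis, with disability defined.
- For women lost in pregnancy, do not call the resulting set intention-to-treat. State that their outcome is missing.
- Report losses in pregnancy, and pregnancy losses and still-births, by arm.
- Add a sensitivity analysis that counts women lost with a known or presumed live birth as not exclusively breastfed. The choice of any imputation model can stay with the SAP.
- Correct the limitations paragraph: neither intention-to-treat nor the sample-size allowance removes bias from loss. Align the Statistical analysis section with it.

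The cost is a few sentences of wording, two sensitivity analyses and a participant-flow table by arm. Recruitment is unaffected, and baseline data are already collected at recruitment. Pairs with a disabled child need only stay in the planned follow-up.
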